**Methods:**

Participants will be recruited during face-to-face visits and randomized to either an interventional (ie, HealthPROMISE) or control (ie, education app). Patients in the HealthPROMISE arm will be able to update their information and receive disease summary, quality metrics, and a graph showing the trend of QOL (SIBDQ) scores and resource utilization over time. Providers will use the data for collaborative decision making and quality improvement interventions at the point of care. Patients in the control arm will enter data at baseline, during office visits, and at the end of the study but will not receive any decision support (trend of QOL, alert, or dashboard views).

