**Results:**

Enrollment in the trial will be starting in first quarter of 2015. It is intended that up to 300 patients with IBD will be recruited into the study (with 1:1 allocation ratio). The primary endpoint is number of quality indicators met in HealthPROMISE versus control arm. Secondary endpoints include decrease in number of emergency visits due to IBD, decrease in number of hospitalization due to IBD, change in generic QOL score from baseline, proportion of patients in each group who meet all eligible outpatient quality metrics, and proportion of patients in disease control in each group. In addition, we plan to conduct protocol analysis of intervention patients with adequate HealthPROMISE utilization (more than 6 log-ins with data entry from week 0 through week 52) achieving above mentioned primary and secondary endpoints.

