## Methods

### Study Design

This is a phase III, single-center, pragmatic randomized controlled trial (RCT) to evaluate if a patient-centric self-monitoring and collaborative decision support platform will lead to sustainable improvement in overall QOL for IBD patients. It is intended that 300 patients with IBD will be recruited into the study (allocation ratio 1:1; Figure 4). After meeting all the inclusion criteria with no exclusions, patient is asked to complete a tablet-based screening questionnaire at the end of which patient is randomized at the point of care to intervention or control arm. Patients in the control arm will receive an IBD education app PIN whereas the intervention arm will receive HealthPROMISE app PIN (Figure 3). Intervention patients enter their data once every 2 weeks and this data is then made visible to providers using a Web-based dashboard integrated with the EHR (Figures 4 and 5). Intervention and control apps will be provided free of charge to patients, and patients will be given $25 after completing initial and end of study questionnaires.

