#### Other Instruments

eHEALS is an 8-item measure of eHealth literacy developed to measure consumers’ combined knowledge, comfort, and perceived skills at finding, evaluating, and applying electronic health information to health problems [22]. This instrument has been psychometrically validated and its score positively correlated with intention to use personal health records. Patient Activation Measure (PAM-13) will be used to measure patient activation and engagement with health [23]. eHEALS and PAM-13 will be completed by patients in both arms during entry and exit surveys only.

Quality indicators are included from a list of indicators published by national societies and finalized through a Delphi panel of IBD providers [24,25]. These will be updated every three months by either providers or patients, along with hospitalization and emergency department visit information (Figure 7).

Utilization will be assessed through log-in, page views, health information updates, and response to alerts and reminders.

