## Results

### Outcome Measures

All outcome data (Textbox 1) will be collected online. Additionally, we will conduct subgroup analysis of patients with poor disease control at week 0 (SIBDQ≤30) and in those with high patient-reported anxiety, depression, or stress achieving primary and secondary endpoints. We will assess change in inflammatory markers, endoscopic scores, and additional quality metrics in each group and determine predictors of HealthPROMISE and control app utilization and its impact on other primary and secondary end-points. Consistent with the pragmatic nature of the trial, study progress will be assessed throughout and effort will be optimized to better engage providers and patients (Table 1).

Primary and secondary endpoints.Primary endpointNumber of quality indicators met in HealthPROMISE versus control armSecondary endpoints
_Decrease in number of emergency visits due to IBD_

_Decrease in number of hospitalization due to IBD_

_Change in generic QOL score (EQ-5D) from baseline_

_Proportion of patients in each group who meet all eligible outpatient quality metrics_

_Proportion of patients in disease control in each group_

_Emergency visits in each group_

_Hospitalizations in each group_

_General QOL scores in each group_

_Per protocol analysis of intervention patients with adequate HealthPROMISE use (more than 6 log-ins with data entry from week 0 through week 52) achieving above mentioned primary and secondary endpoints_

**Table 1 table1:** Evaluation metrics for HealthPROMISE progress

Metric		Target Group	Goal / Timeline

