#### Sample Size Justification

Study endpoints will be primarily assessed using intention-to-treat (ITT) analysis; however, per-protocol analysis will also be performed. The study is to be powered such that there is a>80% probability of demonstrating a difference with a *P* value *(P* = .05) using a two-tailed *t* test.

We assume that 128 out of 150 subjects (85%) in the intervention arm will meet all quality indicators (primary outcome) and expect that this percentage will be at least 15% lower in the control arm. A sample size of 95 patients will be needed in each arm to achieve at least 80% power to detect the difference with a 5% one-sided significance level.

Accounting for an estimated 30% attrition rate, we will require a total of 250 IBD patients to be enrolled in the study. Since some patients may agree to enroll but not download the app or use the PIN, we will recruit a total of 300 patients in the study.

For secondary outcomes related to QOL, the control arm is not a placebo arm and physicians are free to initiate any therapy based on patients' symptoms. Hence, we will assess the difference in proportion of patients achieving MCID in the HealthPROMISE arm versus control arm in the study. Using the distribution-based approach, an effect size of 0.5 SD is the closest estimate for determining MCID for SIBDQ and EQ-5D. Assuming that 20% more patients in HealthPROMISE arm will achieve MCID than in the control arm, the sample size of 250 patients will have 88% power to detect the difference with a 5% one-sided significance level and an estimated 30% attrition rate.

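### The per-protocol analysis selects intervention patients by their app use after randomization, has no control-arm counterpart or named comparator, and is listed as a secondary endpoint covering all outcomes

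*Protocol article*

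**What the plan says.** The Outcome Measures section (Textbox 1) ends its list of secondary endpoints with a "Per protocol analysis of intervention patients with adequate HealthPROMISE use (more than 6 log-ins with data entry from week 0 through week 52", to be assessed on patients "achieving above mentioned primary and secondary endpoints". The Results paragraph of the abstract repeats the rule, again for intervention patients only. Sample Size Justification makes intention-to-treat primary and adds that "per-protocol analysis will also be performed".

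The arms have different data-entry schedules. Study Design says "Intervention patients enter their data once every 2 weeks". The abstract's Methods paragraph says "Patients in the control arm will enter data at baseline, during office visits, and at the end of the study".

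Two further statements bear on the point. Of the quality indicators, Other Instruments says: "These will be updated every three months by either providers or patients". Outcome Measures also plans to "determine predictors of HealthPROMISE and control app utilization", and to examine how use relates to the endpoints. Control-app use is therefore recorded, but it does not define a per-protocol set.

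**The concern.** A per-protocol set is normally defined in both arms. Here the filter is a behaviour shown during follow-up in one arm, so it removes the less engaged intervention patients and leaves the control arm whole. The less engaged controls, who would have failed the same filter, stay in the comparison. Any difference in prognosis between engaged and less engaged patients then appears as a difference between arms.

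The article itself treats use as non-random: it plans to look for predictors of it, and it collects eHealth literacy (eHEALS) and patient activation (PAM-13) at entry. Because patients may update the quality indicators themselves, frequent data entry could also raise the number recorded as met without any change in care.

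At stake is a listed secondary endpoint, repeated for every outcome, that would either have no comparator or have one not protected by randomization.

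**Working it through.** **Inputs from the article.** 300 patients, 1:1, so 150 per arm (Study Design). 30% attrition: 150 × 0.70 = 105 per arm. Intervention rate 85%, control rate 15 points lower, so 70% (Sample Size Justification). Enrolment is raised from 250 to 300 because some patients may not download the app or use the PIN: 250/300 = 83%. The use threshold is at least 7 log-ins in weeks 0 to 52, against about 26 fortnightly entries: 7/26 = 27%.

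**The plan's own figure.** With a one-sided 5% level, 80% power and a pooled variance without continuity correction, n = [1.645 × √(2 × 0.775 × 0.225) + 0.842 × √(0.85 × 0.15 + 0.70 × 0.30)]² / 0.15² = 94.8, so 95 per arm. This matches the article. It does not bear on the per-protocol analysis, but it confirms the reading of 70% as the control rate.

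**Assumptions not in the article.** The share *f* of the intervention arm with adequate use, and the correlation *r* between engagement and outcome. I take *f* = 50%, 70% and 83% (the last borrowed from the enrolment allowance) and *r* = 0.2 and 0.3.

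**Model with no app effect.** Engagement E and latent outcome Y are standard normal with correlation *r*. Success is Y > −0.524, which gives 70% in both arms. Adequate use is E above its (1 − *f*) quantile c. Then:

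- users' success rate: p = P(E > c, Y > −0.524) / *f*
- spurious difference: d = p − 0.70, which equals (1 − *f*) × (users' rate − non-users' rate)
- users n = *f* × 105, controls 105; SE0 is the pooled and SE1 the unpooled standard error
- rejection in favour of the app: Φ((d − 1.96 × SE0) / SE1), nominal 2.5%

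**One row in full** (*f* = 50%, *r* = 0.3). p = 0.784 and d = 0.084 with 52 users. The pooled rate is (52 × 0.784 + 105 × 0.70)/157 = 0.728. SE0 = √(0.728 × 0.272 × (1/52 + 1/105)) = 0.0755. SE1 = √(0.784 × 0.216/52 + 0.21/105) = 0.0725. Rejection = Φ((0.0842 − 0.1480)/0.0725) = Φ(−0.88) = 19.0%.

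| Adequate use | r | Users | Controls | Spurious gain | Rejection for the app |
|---|---|---|---|---|---|
| 50% | 0.2 | 75.6% | 70% | 5.6 points | 10.4% |
| 50% | 0.3 | 78.4% | 70% | 8.4 points | 19.0% |
| 70% | 0.2 | 73.6% | 70% | 3.6 points | 7.3% |
| 70% | 0.3 | 75.5% | 70% | 5.5 points | 12.0% |
| 83% | 0.2 | 72.2% | 70% | 2.2 points | 5.2% |
| 83% | 0.3 | 73.4% | 70% | 3.4 points | 7.5% |

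**Opposite sign.** With *r* = −0.2 and 50% adequate use, users reach 64.4%, which is 5.6 points below controls, and rejection for the app falls to 0.4%.

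**How far selection would have to go.** To produce the whole planned 15 points at *f* = 50%, users and non-users would have to differ by 0.15/0.50 = 30 points. That lies outside the range assumed above, where the gap at *f* = 50% is 11 to 17 points.

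**The case against.** The strongest reply is that intention-to-treat governs and the per-protocol analysis is only additional. That stands. A reader might infer that the trial's main result is compromised, or that this analysis could replace it; nothing in the article supports either.

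Next, no comparator is named. Read literally, the item may be a within-arm description of adequate users, for which a rejection rate means nothing. That stands too, so the figures above are conditional on a comparison with all controls. It does not rescue the item as a secondary endpoint: a description of one selected subgroup is not a comparison of arms. Nor is this detail left to a fuller document, since the article itself fixes the one-arm rule and its place in the list.

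Several stronger readings are tempting but not supported:

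- *Control use is unobserved.* Control-app use is to be analysed, and eHEALS and PAM-13 are collected in both arms. What is missing is an equivalent of the data-entry rule, because controls are not asked for fortnightly entries.
- *The criterion is circular.* Only in part: providers as well as patients update the indicators, and the SIBDQ is completed at baseline and exit in both arms.
- *The plan expects substantial non-use.* It says only that some patients may not take up the app, and the threshold is low at about 27% of scheduled entries.
- *The bias must favour the app.* It reverses if sicker patients log in more.

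Finally, the weeks 0 to 52 window can be defended. After a positive interim analysis all patients are offered the app, so only the first year has an assured contrast between arms. That is fair, but the percentage score is defined as a change to week 104 (Statistical Analysis Plan, Overview), so window and outcome still need to be aligned.

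**Conclusion.** The point holds for a secondary analysis and goes no further. The rule as written selects on post-randomization behaviour in one arm, names no comparator, and is listed as a secondary endpoint for all outcomes. If adequate users are compared with all controls and the app has no effect, the spurious gain is about 2 to 8 points and rejection in favour of the app about 5% to 19% instead of 2.5%. This rests on 70% success, 105 per arm, adequate use of 50% to 83% and a correlation of 0.2 to 0.3; the article gives neither of the last two. The size falls as adequate use rises, vanishes if engagement is unrelated to outcome, and changes sign if sicker patients use the app more. The primary intention-to-treat conclusion is untouched.

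**What to change.** Remove the item from the secondary endpoint list and report outcomes in adequate users as descriptive only, without a test against controls.

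If an effect of use is wanted, estimate a complier-average causal effect:

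- Use randomization as the instrument, retain both randomized arms, and handle missing outcomes as in the intention-to-treat analysis.
- State the exclusion restriction: assignment has no effect on patients who do not reach the threshold. This is doubtful at more than 6 log-ins, because data from patients with 1 to 6 log-ins also reach providers on the dashboard. If the effect is a in adequate users and b in the others, the estimate is [*f*·a + (1 − *f*)·b]/*f* = a + b(1 − *f*)/*f*; at *f* = 50% it overstates a by the whole of b.
- Vary the threshold, at least any use against more than 6 log-ins.
- Match the use window to the outcome time point. If the app is offered to controls after the interim analysis, their use must be counted too when the outcome is at week 104.

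The cost is small: log-ins are already recorded. The drawbacks are a wider interval than the naive comparison gives, and an estimate that is inflated if use below the threshold has a beneficial effect.

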**Process**			
	Number of providers trained	Investigators	10 in 2 months
	Number of patients enrolled	Participants	300 in 6 months
	Recruitment and training of key personnel	Coordinator	1 in 3 months
	Patient utilization of HealthPROMISE	Participants	Ongoing
	Provider utilization of HealthPROMISE	Providers	Ongoing
	Response to alert within 2 business days	Providers	>90%
**Outcome**			
	Improvement in quality of care metrics	Provider, Center	Quarterly reports
	Improvement in quality of life	Provider, Center	Quarterly reports
	Readmission rate in two arms	Provider, Center	Quarterly reports

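### Table 1 schedules a quarterly readmission report split by arm, with providers and the center as target group, while providers still treat patients and may record outcomes

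*Protocol article*

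**What the plan says.** Table 1 of the protocol article (Results, Outcome Measures) lists evaluation metrics under three columns: metric, target group, and goal or timeline. Its outcome block has three rows: quality of care ("Improvement in quality of care metrics"), quality of life, and "Readmission rate in two arms". All three carry the target group "Provider, Center" and the timeline "Quarterly reports". Only the readmission row is stated by arm.

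The Outcome Measures text that cites the table says that "study progress will be assessed throughout and effort will be optimized to better engage providers and patients".

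Other Instruments says of the quality indicators: "These will be updated every three months by either providers or patients, along with hospitalization and emergency department visit information". The abstract fixes the primary endpoint: "The primary endpoint is number of quality indicators met in HealthPROMISE versus control arm". Interim Analysis plans one formal look, when 150 patients have reached week 52.

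**The concern.** A between-arm outcome comparison that circulates during follow-up can change the conduct of the trial if it reaches people who treat patients or record outcomes. They may work harder for the arm that seems to lag, engage more with the arm that seems to lead, or record events and indicators more completely in one arm. A final comparison of the arms cannot separate such shifts from the effect of the app. For this reason comparative interim data are normally kept from treating and recording staff. Here the schedule for the by-arm report is printed in the plan, so the point does not rest on a missing detail.

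**Working it through.** The point rests on no figure in the plan, so the check sets the article's statements side by side.

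1. **What is scheduled.** One outcome row of Table 1 is a randomized comparison (readmission), reported quarterly. With 13 weeks to a quarter, that is 52/13 = 4 reports by week 52 and 104/13 = 8 by week 104. Interim Analysis plans a single formal look.

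2. **What the table is used for.** Outcome Measures cites Table 1 in the sentence on assessing progress and adjusting effort during the trial. The table is thus presented as a working tool during follow-up as well as a list for the final report.

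3. **Who is named.** Providers and the center are the only parties named on the readmission row. A report needs a reader, and no other reader is given.

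4. **What providers know.** Study Design says that intervention patients' data appear on a provider dashboard linked to the health record. Providers can therefore tell who uses the app.

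5. **What providers can influence.** The abstract's Methods says that providers act on these data when they see patients. Other Instruments lets either providers or patients update the indicators, hospitalizations and emergency visits every three months, the same interval as the reports. Some of the people named on the by-arm row may therefore both deliver the care and record the primary outcome and the hospitalization data.

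6. **Whether the arms are separated by provider.** Randomization is by patient at a single center (Study Design), and the analysis section describes patients as nested within physicians. The article describes no split of providers by arm.

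Taken together, steps 1 to 6 give a route from an accumulating between-arm result to care, effort and recording.

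**Size.** The article gives no expected readmission rate, no share of indicators updated by providers, and no basis for how far behavior would move. A bias could be computed only by assuming a shift, and the answer would then be the assumption. The direction is open too: extra effort for the app arm would exaggerate the difference, and extra effort for control patients would shrink it.

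**The case against.** The strongest objection concerns the column heading, Target Group. In the process rows that column names whoever is measured or aimed at: participants for enrollment, the coordinator for recruitment of personnel, providers for alert response. Read in that way, "Provider, Center" is the level at which readmission is summarized, and nothing says that treating providers receive the report. This stands as a possible reading, so receipt by providers must be put as the natural reading and not as a stated fact. It does not remove the point: on either reading a by-arm outcome report is scheduled every quarter during follow-up, and the table should say who sees it.

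Several further objections stand and limit the point:

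- A reader might infer that the primary endpoint is also reported by arm each quarter. The document does not support this. The quality-of-care and quality-of-life rows state no split, and readmission is neither the primary endpoint nor a secondary endpoint in those words, although hospitalization is.
- A reader might treat the quarterly reports as repeated significance tests and calculate an inflated false-positive rate. No report is said to trigger a decision. The only decision rule belongs to the interim analysis of the primary outcome, so such a figure does not apply.
- The adjustment of effort is described in terms of engaging providers and patients, which the process rows already track. Nothing says that between-arm outcomes will drive it. They do, however, sit in the table cited for that purpose.
- Providers would know who uses the app without any report, and feedback on individual patients through the dashboard is part of the intervention. Only the comparative, aggregate result is avoidable.

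A journal article may leave report distribution lists to the full protocol, and their absence is not criticized here.

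**Conclusion.** The point holds in a limited form. Table 1 schedules one between-arm outcome report, on readmission, every quarter, with providers and the center as its target group. On the most natural reading, people who treat patients and may record outcomes would see it. That is an avoidable route to operational bias. Its size cannot be quantified from the document and its direction is not determined.

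The conclusion rests on two assumptions: that Target Group includes those who see the report, and that the article's description of providers' roles applies to the providers named in the table. If the full protocol already restricts access, what remains is to align the table with it. The point does not show that by-arm results on the primary endpoint are fed back, or that the type I error is inflated.

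**What to change.** In Table 1, change the readmission row to a rate pooled over both arms for any report that providers or the center see during follow-up, and state that the quality-of-care and quality-of-life reports are likewise not split by arm. Reserve by-arm outcome data for the planned interim and final analyses, handled by someone who neither treats patients nor records indicators. Base any adjustment of effort on the process rows of the same table: enrollment, training, utilization and alert response.

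The cost is an edit to the table and the report template. The downside is that the center will not see by-arm outcomes during follow-up. The change does not stop pooled quality feedback from reaching the providers of control patients; it removes only the comparison between arms.
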